#### Definition of dataset analysed

A per-protocol and an intention-to-treat analysis will be performed, and only if both approaches support non-inferiority will the trial be considered as supporting our non-inferiority hypothesis.

### Reporting of adverse events

Participants are asked about any side effect including (serious) adverse events immediately and 2 days postoperatively. All these events are recorded and monitored until the patient has completely recovered or until no causal relationship to the study drug administration has been established. All serious adverse events will be reported to the Ethics Committee and the sponsor within the appropriate time frame.

The trial will be terminated early in the event of relevant safety concerns that threaten the study participants in any way. Therefore, we will monitor the incidence of PPH in a blinded manner and stop the study early for safety concerns if the incidence rate should rise above the average value of about 5 % PPH in CS [20].

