## Background

Uterotonic drugs are routinely used after caesarean section (CS) to reduce blood loss and the risk of postpartum haemorrhage (PPH) [1]. PPH is defined as a blood loss of at least 500 ml after vaginal birth and at least 1000 ml after CS and/or the need for blood transfusion within 24 hours after delivery [2, 3] and represents the most important cause of maternal morbidity [4]. As PPH is more common after CS than after vaginal delivery [5] and as the rate of CS is rising, the incidence of PPH is expected to increase accordingly.

The two most commonly used uterotonic drugs after operative delivery are oxytocin and carbetocin, a synthetic oxytocin analogue. Carbetocin has some advantages over oxytocin due its four- to ten-times longer half-life [6], allowing for a single injection. Moreover, a recent meta-analysis showed that carbetocin significantly reduces the use of additional uterotonics as compared to oxytocin, although the risk of severe PPH remains similar [7].

Carbetocin is associated with cardiovascular side effects including hypotension and a compensatory increase in heart rate similar to those of oxytocin [8, 9]. According to randomised trials with oxytocin, the extent of these cardiovascular side effects seems to be dependent on dose [10, 11] and the rate of administration [12]. The manufacturer of oxytocin requires the drug to be given as a short-infusion to maintain cardiovascular stability. In contrast, the manufacturer of carbetocin recommends a bolus injection of carbetocin. Whether carbetocin administration as short-infusion offers the optimal balance between contractile benefit to minimise maternal haemorrhage and reduce cardiovascular side effects is unclear.

In this randomised controlled trial, we aim to investigate whether carbetocin 100 mcg applied as a short-infusion in 100 ml 0.9 % sodium chloride as compared to a bolus injection minimises the cardiovascular side effects (first secondary safety endpoint) without compromising uterine tone (primary efficacy endpoint) in women undergoing a planned or unplanned caesarean delivery.

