## Methods/Design

### Study design and setting

This is a prospective, single-centre, randomised, double-dummy, investigator-initiated, non-inferiority trial conducted at the University Hospital Basel, Switzerland. Study recruitment commenced in December 2014 and is expected to last for 16 months. The study was approved by the regional Ethics Committee (Ethikkommission Nordwestschweiz (EKNZ), EKNZ 2014–088, 13 March 2014). The study was registered in a national and an international trial registry (www.kofam.ch SNCTP000001197 and clinicaltrials.gov NCT02221531).

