#### Data monitoring and stopping rules

The Ethics Committee agreed that monitoring would be performed by the interdisciplinary study team. This team will evaluate the progress of the trial, verify the accuracy and completeness of the case report forms (CRFs), and ensure that all protocol requirements and investigator’s obligations are being fulfilled. The progress of the trial is evaluated every second month. The overall distribution of uterine tone will be assessed after 2 and 8 months in a blinded way, i.e. without considering group allocation. Extreme values are investigated further by reviewing the intraoperative course and by determining reasons for low uterine tone.

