### Choice of primary endpoint

We consider the choice of the appropriate measurement of our primary endpoint as a main challenge in this trial. The choice of our primary outcome is based on a randomised controlled trial performed by Butwick et al. [11] who also used a LAS ranging from 0 to 10 to assess uterine tone in a similar setting. We expanded the scale from 0 to 100 to avoid the fact that some outcome assessors used decimal places (e.g. 7.5) while others did not. Moreover, manual palpation of the uterus represents the standard method to assess uterine tone in daily clinical practice. To reduce bias, especially when using a subjective primary outcome measurement, we have established and will maintain blinding by using a double-dummy technique for study drug administration in patients and all care providers until the statistical analysis has been performed. We have chosen to abstain from a binary assessment of the uterine tone as it would be too parallel to our secondary outcome variable ‘any additional uterotonics – yes/no’. The objective efficacy outcome of interest would have been intraoperative blood loss. Blood loss during PPH is often estimated visually, but visual assessment has been shown to be imprecise, usually underestimating blood loss particularly concerning larger volumes [21–24]. We have, therefore, decided to choose the uterine tone as our primary outcome variable. We consider blood loss as a secondary endpoint, calculated by taking into account the pre- and postoperative haematocrit and the estimated blood volume of the parturient [15].

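### The PPH safety rule stops the trial at its own background rate of about 5%, with no allowance for chance, so a trial without excess PPH has a high chance of being stopped

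*Protocol article*

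**What the plan says.** The rule is in the protocol article under Reporting of adverse events. The sponsor writes "we will monitor the incidence of PPH in a blinded manner" and will "stop the study early for safety concerns if the incidence rate should rise above the average value of about" 5%, given there as the average for PPH at caesarean section. The section gives no confidence bound, margin or other allowance for chance around that value.

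Three other places bear on how the rule would work:

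- Data monitoring and stopping rules says "The progress of the trial is evaluated every second month". This concerns trial progress in general, not PPH. The same section explains blinded review, there of uterine tone, as "in a blinded way, i.e. without considering group allocation". I read the PPH rule the same way, as one rate pooled over both arms.
- Study design and setting: "Study recruitment commenced in December 2014 and is expected to last for 16 months". Trial status reports an average of three patients a week and 60% enrolled at submission.
- Background defines PPH after caesarean section as "at least 1000 ml after CS and/or the need for blood transfusion within 24 hours after delivery".

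**The concern.** A safety threshold is normally set far enough above the expected rate that chance alone seldom reaches it. Here the threshold and the expected rate are the same number, and the comparison is of a raw proportion. Early on, one case is enough: 1/19 = 5.3% is above 5%, and so is one case among any smaller number of women.

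The rule therefore leads to one of two outcomes. If followed literally, it is likely to end a trial with no excess PPH before the 126 evaluable women needed for the primary comparison are reached. If set aside when it is met, the trial departs from its published safety commitment. In either case a crossing carries little information. Choice of non-inferiority design gives blood loss as the underlying worry with the infusion, yet a pooled rate cannot say which arm an excess comes from.

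**Working it through.** **Inputs.** Threshold about 5%, pooled (Reporting of adverse events). Total of 140 patients (Sample size justification). Allocation 1:1 (Randomisation and blinding). Recruitment over 16 months, or three patients a week. The article states no error rate for the PPH rule, so there is no such figure to reproduce.

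**Check of the total.** With SD 20, margin 10, one-sided 2.5% and 80% power, n per group = 2 × (1.960 + 0.842)² × 20² / 10² = 62.8, so 63. Then 126 / 0.90 = 140. The stated total is reproduced.

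**Look schedules (assumption: PPH is checked at the two-monthly reviews).**
- 8 looks: 16 months / 2 = 8, and 140 / 8 = 17.5 patients per look, giving n = 18, 35, 53, 70, 88, 105, 123, 140. The rule is met at 1, 2, 3, 4, 5, 6, 7 and 8 cases.
- 5 looks: three a week is about 26 per two months, giving n = 26, 52, 78, 104, 130. The rule is met at 2, 3, 4, 6 and 7 cases.

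**Single looks, true rate 5%.**
- n = 18: P(at least 1 case) = 1 − 0.95^18 = 1 − 0.397 = 0.603. One case is 5.6%.
- n = 70: P(at least 4 cases) = 0.466.
- n = 140: P(at least 8 cases) = 0.401. This look comes too late to stop the trial early.

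**Repeated looks.** The exact binomial distribution of the case count is carried forward patient by patient. At each look, the probability of being above 5% is removed and added to the stopping probability.

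| True rate, both arms | 8 looks | 5 looks |
|---|---|---|
| 5% | 80% | 71% |
| 4% | 68% | 53% |
| 3% | 53% | 34% |
| 2% | 35% | 16% |

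Without the last of the 8 looks, the 5% figure is 79%. With looks only at n = 70 and n = 140 it is 56%.

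**Harm in one arm, 8 looks.**
- 5% versus 10% (pooled 7.5%): 96%.
- 5% versus 15% (pooled 10%): 99.5%.
- 2.5% versus 7.5%, or 2% versus 8% (pooled 5%): 80%, the same as 5% in both arms.

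**A bound that allows for chance (illustration).** Stop at a look only if the exact one-sided binomial p-value against 5% is at or below a set level. At 2.5% per look, the 8-look boundaries are 4/18, 6/35, 7/53, 8/70, 10/88, 11/105, 12/123 and 13/140. At 1% they are 5/18, 6/35, 8/53, 9/70, 11/88, 12/105, 13/123 and 15/140.

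| Probability of a stop, 8 looks | True 5% | Pooled 7.5% | Pooled 10% |
|---|---|---|---|
| Rule as written | 80% | 96% | 99.5% |
| 2.5% per look | about 5% | 33% | 71% |
| 1% per look | 2% | 19% | 55% |

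**The case against.** **The schedule and the true rate are assumptions.** The article gives no timetable for PPH checks, and a condensed article may leave it to the full protocol. Entry is limited to healthy women with a singleton at term. Emergency sections, unplanned sections for fetal distress, (pre-)eclampsia and coagulopathies are excluded, so a rate below the average is plausible. At 3% with 5 looks the chance of crossing is 34%, and with looks at n = 70 and 140 only it is 18%. This stands. A reader might infer that a safe trial is stopped more often than not whatever the circumstances. That holds only for repeated checks and a true rate near 5%. The threshold itself, however, is stated in full, and no look schedule adds an allowance for chance to it.

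**Harm is not hidden.** A reader might infer that harm in one arm would go unseen. The figures do not support that: harm added to a 5% background raises the pooled rate and nearly always crosses. What is true is narrower. A crossing is weak evidence of harm, it names no arm, and an imbalance averaging 5% looks like none. Serious adverse events also go to the ethics committee and the sponsor.

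**PPH is defined.** A reader might infer from the remark that "visual assessment has been shown to be imprecise, usually underestimating blood loss" that the rule has no usable endpoint. Background defines PPH after caesarean section, and that remark explains why calculated blood loss was preferred. Which measurement feeds the rule is detail that an article may omit.

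**Limited damage.** A stop on pooled blinded data does not bias the treatment comparison. With 60% enrolled, the full-trial probabilities also overstate the remaining risk. Both points stand and lower the severity.

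**Conclusion.** The point holds. The stopping threshold equals the article's own expected rate and allows nothing for chance. Assuming a true 5% in both arms and two-monthly checks, the chance that a trial with no excess PPH meets the rule is about 80% (8 looks) or 71% (5 looks), and 47% at one look at n = 70. At a true 3% the two schedules give 53% and 34%. The rule is highly sensitive but barely specific: with 8 looks, 96% for 5% versus 10% against 80% for no harm. It should be fixed, but it is not critical: the risk is a needless loss of sample size or a disregarded safety rule, not a biased result.

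**What to change.** Amend Reporting of adverse events in two respects, keeping 5% as the reference rate:

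1. A raw pooled rate above 5% triggers a safety review, not an automatic stop.
2. The stop rests on statistical evidence that the rate exceeds 5%, for example an exact one-sided binomial bound at each look, with the looks listed and the false-stop and detection probabilities stated.

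The administrative cost is a short amendment and a notice to the ethics committee. The real cost is sensitivity to a moderate excess. With 8 looks, a pooled 7.5% would stop 33% of trials under a 2.5% per-look bound and 19% under a 1% bound, against 96% now. At a pooled 10% the figures are 71% and 55%, against 99.5%. The review in step 1 has to carry that gap, and the amendment should say so. The sponsor and the ethics committee should choose the level with these figures before them.

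Pooled data will still not attribute an excess to an arm. A by-arm review would, but it needs an additional unblinded person, so it is an option for the sponsor to weigh and not part of the minimum change.

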## Discussion

This randomised controlled investigator-initiated trial prospectively evaluates how the uterine contractility and haemodynamic parameters are affected by the mode of administration of carbetocin in patients undergoing a CS. Based on the findings of reduction in cardiovascular side-effects with a short-infusion as compared to a bolus injection found for oxytocin [12], our study hypothesis is that a slower administration rate of carbetocin (using a short-infusion) minimises cardiovascular side effects without compromising uterine tone. In the following, we discuss considerations regarding trial design and chosen endpoints.

### Choice of non-inferiority design

The aim of this trial is to reach greater haemodynamic stability using the slower administration method (primary safety endpoint) while ensuring non-inferiority with regard to the uterine tone (primary efficacy endpoint) and ultimately the risk of elevated blood loss. Since superiority in haemodynamic endpoints can be achieved with fewer patients, we decided to choose as our primary endpoint non-inferiority in uterine tone.

### Choice of primary endpoint

We consider the choice of the appropriate measurement of our primary endpoint as a main challenge in this trial. The choice of our primary outcome is based on a randomised controlled trial performed by Butwick et al. [11] who also used a LAS ranging from 0 to 10 to assess uterine tone in a similar setting. We expanded the scale from 0 to 100 to avoid the fact that some outcome assessors used decimal places (e.g. 7.5) while others did not. Moreover, manual palpation of the uterus represents the standard method to assess uterine tone in daily clinical practice. To reduce bias, especially when using a subjective primary outcome measurement, we have established and will maintain blinding by using a double-dummy technique for study drug administration in patients and all care providers until the statistical analysis has been performed. We have chosen to abstain from a binary assessment of the uterine tone as it would be too parallel to our secondary outcome variable ‘any additional uterotonics – yes/no’. The objective efficacy outcome of interest would have been intraoperative blood loss. Blood loss during PPH is often estimated visually, but visual assessment has been shown to be imprecise, usually underestimating blood loss particularly concerning larger volumes [21–24]. We have, therefore, decided to choose the uterine tone as our primary outcome variable. We consider blood loss as a secondary endpoint, calculated by taking into account the pre- and postoperative haematocrit and the estimated blood volume of the parturient [15].

### Haemodynamic measurement method

We chose haemodynamic stability, defined as lowest mean arterial pressure and highest heart rate within the first 5 minutes after the administration of the carbetocin. After evaluating the options for continuous invasive and non-invasive blood pressure measurements, we have decided to measure blood pressure non-invasively using a cuff on the upper arm. We have considered the accuracy and the precision of the continuous non-invasive methods insufficient to justify their use in the context of this trial. Although the risk for complications of an intra-arterial catheter is low [25], the potentially severe side effects do not justify invasive blood pressure monitoring.

This sample size allows showing a superiority of the short-infusion over the bolus administration in mean arterial blood pressure by at least 5 mmHg with 80 % power and a type-1 error of 5 % assuming a SD of 10. Thus, even a clinically irrelevant difference in efficacy could be found with our data. However, we need to acknowledge that we are not able to show a minor difference in the incidence of serious drops in blood pressure with our sample size.

### Choice of study population

This trial will include patients undergoing a planned and an unplanned CS. Patients undergoing a unplanned CS often have already received oxytocin to induce or enhance labour, thus, showing a different response to the intraoperative dosage of carbetocin. Therefore, we are using a stratified randomisation for planned and unplanned CS. Excluding these patients would limit the generalisability of our study results.

### Recruitment

Poor recruitment is the most frequently reported cause for discontinuation of a clinical trial [26]. However, due to good interdisciplinary cooperation, adequate personal and financial resources and a high acceptance for clinical research, we are able to exceed the target recruitment rate (Fig. 2). Additionally, an amendment was handed in shortly after the beginning of the recruitment to incorporate patients with a breech position fetus. Within the same amendment, we have also translated the study information and the consent into English to be able to address more patients.

**Fig. 2 Fig2:**
[figure not shown]
Target and actual recruitment rate to achieve the given sample size within the planned recruitment period

### Implications for future clinical practice

Haemodynamic stability and adequate uterine contractility are important outcomes in CS. The results of this trial may be used to optimise these factors and thereby increase safety in parturients due to reduced cardiovascular side effects.

## Trial status

The trial is currently enrolling patients. Upon submission of this manuscript, 60 % of the patients have been enrolled. The average enrolment rate is three (range one to seven) patients every week.

## Abbreviations

CI: confidence interval
CONSORT: Consolidated Standards of Reporting Trials
CS: caesarean section
GEE: generalised estimation equation
LAS: linear analogue scale
PPH: postpartum haemorrhage
SD: standard deviation
